## Background

Neophobia or new food refusal (ranging from severe rejection to a moderate manifestation) is a common behaviour in children and should be carefully considered due to the important implications on the current and future health status of the infants [1–3]. Parents, caregivers and health professionals are concerned about infant food neophobia and picky eating, since it can derive in an inadequate diet [4, 5]. The American Psychiatric Association described food neophobia as ‘avoidance and/or restriction to food based on the extreme sensitiveness to the appearance, colour, smell, texture, temperature or taste’ [6]. Hay et al. [7] described a 0,3% prevalence in the Australian population over 15 years of age and showed an association to socio-economic disadvantaged groups and obesity. Although there is limited prevalence data, it is known that clinically significant feeding and eating difficulties are common in early childhood, with estimates of 5–25% in young children [1, 8]. Neophobia has been linked to poor growth and deficient development [9, 10]. Moreover, childhood constitutes the key period in which feeding behaviour is established and then maintained up to adulthood [11, 12]. This is the reason why many authors highlight the relevance of addressing neophobic behaviour since childhood [13].

Fruits and vegetables (FV) are the main food target in infant food neophobia, because despite their relevant health contribution [14], these are the most commonly rejected foodstuffs and, consequently, they have become a health objective. Nutritional interventions and/or educational programs carried out in the past years have not succeeded to increasing FV intake further than half a portion [15]. According to the literature, fruits are more easily accepted by children than vegetables [16, 17]. There is still a compelling need for a more accurate characterisation of the children’s food consumption profile. National and local dietary surveys, such as the ENALIA Study [18] and the COSI Study [19], and unpublished data from the Vitoria-Gasteiz City Council Nutritional Observatory (2007) showed that only around 20–30% of children follow fruit intake recommendations and around 10% fulfil vegetable intake recommendations. In the view of the above mentioned data, it is plausible to think that FV intake figures will be even lower for neophobic children.

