Regarding the weaning period, a new approach called Baby-Led Weaning (BLW), as opposed to the traditional spoon-feeding (SF), has become popular mostly in the United Kingdom and New Zealand [33]. Actually, regarding the Spanish state, a recent study carried out in Galicia shows a general estimated prevalence of BLW of 14% [34]. Although there is not a clear or precise definition, BLW can be characterized as follows: children are the ones feeding themselves, deciding which will be the rhythm and quantity of food to swallow, using their hands, ingesting pieces of food (not purée, or less than 10% of the total ingested food in purée), sharing family meals, and eating the same family-food [33, 35].

BLW has arisen some concerns on parents, caregivers and health professionals, mainly due to the chocking risk [36]. Nevertheless, some authors have reported no difference on the chocking risk between traditional weaning and BLW [37, 38]. Additionally, there is also a concern about the unfulfilment of the energy requirements of the child [33], particularly regarding initial energy intake. However, the available scientific evidence is not strong enough to support this idea [39]. Among nutrients, iron deficiency is the most generally stated worry [40]. Nonetheless, it has been demonstrated that BLW does not increase iron deficiency nor growth faltering [38]. In any case, children’s diet should be as balanced as possible, in order to fulfil all the nutritional requirements and avoid deficiencies. Some paediatricians have manifested their concern about the possible inappropriateness of food offered to the child when following BLW, stating that meals could be high in fat and too salty [39]. Moreover, allergen intake is also a subject of debate, because food selection is baby-led and this could imply less control over allergen intake in a period when children are more susceptible to food allergens [4]. However, some positive aspects have also been pointed out: usually parents following BLW fulfil WHO (World Health Organization) recommendations regarding the start of complementary feeding at 6 month of age, while SF is associated to an earlier weaning [35]. It has also been observed that when following BLW children develop a better ability for satiety responses [41], which constitutes a protection against obesity. Furthermore, BLW has been related to a greater food variety intake or acceptance [39].

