## Methods

### Hypothesis

A high intake and variety of FV during pregnancy and breastfeeding will lead to distinctive sensorial experiences for the baby, different from the ones whose mothers followed a “standard diet” (SD) (as described in the National Nutrition Surveys). This consumption profile will promote the acceptance of FV along complementary feeding. Additionally, a correct BLW may also contribute to establish healthy eating habits in children.

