### Outcomes

#### Primary outcomes

Change of fruit and vegetable intake: measured by an ad hoc questionnaire reported by parents. At the beginning of the weaning process (depends upon each participant, 4th–6th month) and on the 12th and 18th month after delivery. Prior to the paediatric consultation date, each family will record during 24 h the food intake of the child indicating: the specific food consumed and its composition or commercial brand if necessary; the cooking method; and weight of the food consumed. Three days will be randomly selected within a week, ensuring that two of them are week days and one of them is a weekend day in order to avoid the “day” effect. Families will be provided with informative material on how to perform the measurements and record the information, together with blank forms they need to complete.Change of food acceptance to the exposed FV as the measurement of willingness to eat them: assessed by direct observations of child behaviour (see Fig. 2) and ad hoc questionnaires. Some days after the paediatric control visits on the 6th, 12th and 18th months parents will be contacted by telephone to gather information about foods which might be new for the child and have never been tried before. Any doubts arising on diet or possible recipes are clarified. Parents will be asked to record a video of these mealtimes and send them to the research team. Researchers will explain the video-recording protocol so that it is always recorded following a standard procedure. The Feeding Infants: Behaviour and Facial Expression Coding System (FIBFECS) [59] will be taken into consideration for the analysis of the video recordings. Swallowing times and acceptance or rejection signs will be taken as the main parameters.

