**Fig. 2 Fig2:**
[figure not shown]
General procedure for the child observation events at 6, 12 and 18 months from birth

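### In the visible text each acceptance video uses a fruit or vegetable that the child has not yet tried, and no model carries a food term, so change from 6 to 18 months is confounded with the food tested.

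*Protocol article*

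**What the plan says.** The Primary outcomes section defines the second primary outcome as "Change of food acceptance to the exposed FV as the measurement of willingness to eat them", assessed by direct observation and questionnaires. Some days after the paediatric visits at 6, 12 and 18 months, "parents will be contacted by telephone to gather information about foods which might be new for the child and have never been tried before". Then: "Parents will be asked to record a video of these mealtimes and send them to the research team". What the text standardises is the filming: "Researchers will explain the video-recording protocol so that it is always recorded following a standard procedure". Fig. 2, captioned "General procedure for the child observation events at 6, 12 and 18 months from birth", is not available here.

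Under Statistical analysis, the section on qualitative data compares coded behaviours and expressions by two-way ANOVA between maternal-diet groups or between weaning groups. The section on quantitative data uses linear mixed models with a random intercept for each participant, possibly adjusted for variables that differ at baseline. Neither names the test food or its type as a term.

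The Background states that "fruits are more easily accepted by children than vegetables" and that "BLW has been related to a greater food variety intake or acceptance". The Hypothesis says of high maternal intake: "This consumption profile will promote the acceptance of FV along complementary feeding".

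**The concern.** An acceptance score depends on the child's willingness and on how hard the food is to accept. If the food is not held constant, balanced or modelled, the score mixes the two.

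This matters in two places. Within a child, the food differs at each age, while the outcome is defined as change over those ages. Between groups, the pool of untried foods depends on what the child has already eaten, and the feeding patterns under study may influence that. A group difference in acceptance could then partly reflect a difference in test foods. The choice of food is part of data collection, so analysis can repair it only partly once the videos exist, and not at all if the food was not recorded.

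**Working it through.** **The plan's own figure.** The only calculation in the document is the sample size, set on a different variable: the proportion of children reaching intake recommendations (25% vs 50%, two-sided 0.05, power 80%). With pooled variance, n = [1.96 × √(2 × 0.375 × 0.625) + 0.8416 × √(0.25 × 0.75 + 0.50 × 0.50)]² / 0.25² = 57.7 per group, and 57.7 / 0.8 = 72.1 after 20% dropout, against 72 stated. It reproduces and is not affected by this point.

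**Step 1: change over age.** This needs no assumed number.
- The test food has to be new to the child.
- A food tested at 6 months is no longer new at 12 or 18 months.
- So each child's food changes between visits, even if it comes from a fixed list.
- A participant random intercept removes what is constant within a child. The food varies within a child, so it is not removed. Baseline adjustment does not reach it either, because it arises after baseline. Blind coding of the videos does not change how hard the food is.

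**Step 2: groups at one age.** A bias needs two conditions: the mix of test foods differs between groups, and the foods differ in ease of acceptance. The Background supports the second for fruit against vegetables. It makes the first plausible for weaning method. For maternal diet, the Intervention group section takes mothers above about 414 g/day and encourages them towards 800 g/day. Under Study procedure, intervention groups receive additional diet advice, while control follow-up aims at standard consumption. None of this states which foods a child will have left untried.

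**Step 3: what a difference in mix would do.** Every value here is assumed. Let acceptance of a new fruit be 80% and of a new vegetable 50%, the same in both groups. With vegetable share w, observed acceptance = (1 − w) × 80 + w × 50 = 80 − 30w.

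| Vegetable share, standard group | Vegetable share, more varied group | Observed acceptance | Spurious difference |
|---|---|---|---|
| 50% | 50% | 65% vs 65% | 0 |
| 50% | 60% | 65% vs 62% | −3 points |
| 50% | 80% | 65% vs 56% | −9 points |
| 50% | 40% | 65% vs 68% | +3 points |
| 50% | 20% | 65% vs 74% | +9 points |

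The sign follows whichever mix is assumed. The same formula applies over age: a share moving from 50% to 70% between 6 and 18 months lowers acceptance from 65% to 59% with no change in the child.

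**Step 4: a second illustration, also on assumed values.** Take 40 foods, with 15 tried in the less varied group and 25 in the more varied group, and a true benefit of 0.50 SD. Suppose easier foods tend to be introduced first, with ordering noise equal to the spread of difficulty.

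| SD of food difficulty | Mean difficulty of untried foods, 15 vs 25 tried | Observed benefit | Drift from 6 to 18 months (2 to 25 foods tried) |
|---|---|---|---|
| 0.25 | 0.106 vs 0.175 | 0.43 | 0.16 |
| 0.50 | 0.210 vs 0.350 | 0.36 | 0.31 |
| 1.00 | 0.421 vs 0.701 | 0.22 | 0.63 |

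If the order of introduction is unrelated to difficulty, or both groups have tried equally many foods, the observed benefit stays at 0.50.

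**The case against.** The strongest reply is that Fig. 2 sets out the observation procedure and may restrict the foods. A telephone call asking what is new also fits screening a preset list, and a condensed article may leave the list to the full protocol and further model terms to an SAP. This stands as a limit: the point concerns the visible text only. It does not remove Step 1, because any list that keeps the newness rule still changes the food between visits.

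Second, novelty is what the study measures, and changing foods across visits is common to all groups. This also stands. It spoils the within-child trend as a measure of the child alone, but does not by itself bias a comparison of groups at one age.

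Third, a reader might infer that children with more varied diets are tested on harder leftover foods, so that the test works against the baby-led and high-intake groups. The documents do not support that. No section says in what order foods are introduced, or that untried foods are harder or lean towards vegetables in those groups. If such children met vegetables earlier, their untried foods could lean towards fruit and the bias would reverse.

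**Conclusion.** The point holds in a limited form. On the visible text, change in acceptance from 6 to 18 months is confounded with the food tested, and the stated models cannot separate the two. This rests only on the newness rule and the absence of a food term.

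Bias between groups at one age is possible, not shown. It requires dietary variety, and hence the mix of test foods, to differ by group. Its direction and size cannot be derived from the documents. The 3 to 9 points and the shrinkage from 0.50 to between 0.43 and 0.22 show sensitivity under assumed values and are not estimates for this trial. With equal mixes the bias is zero. The intake outcome and the sample size are unaffected. The change is still worth making, because recording and modelling the food is nearly free.

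**What to change.** 1. Record the test food for every video: fruit or vegetable, and the item.
2. At the existing telephone call, choose where possible one new fruit and one new vegetable per age, taking the first still-untried item from a short ordered list common to all four groups. Do not ask families to hold items back. Sessions are up to about six months apart, and withholding would interfere with shared family meals in the baby-led groups and with intake, the other primary outcome. If Fig. 2 or the full protocol already holds such a list, say so in the text.
3. Analyse fruit and vegetables separately, or add food type as a factor to the ANOVA and the mixed model, with item as a random effect if numbers allow.
4. Base the group conclusion on same-age comparisons, and do not present the trend from 6 to 18 months as change in the child alone.

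Cost: a short list to prepare, some off-list items to handle in a sensitivity analysis, slightly fewer degrees of freedom, and possibly one more recording per age. Without withholding, some imbalance in items within each food type may remain; the record of items lets it be reported.

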**Fig. 2 Fig2:**
[figure not shown]
General procedure for the child observation events at 6, 12 and 18 months from birth

#### Secondary outcomes

Change of maternal diet during pregnancy and breastfeeding: measured by the Predimed questionnaire [60] and the Pre-coded Food Record Form [61]. The Predimed questionnaire has 14 items that evaluate adherence to the Mediterranean Diet, regarded as a good quality dietary pattern. The total score of the questionnaire ranges from a minimum of 0 to a maximum of 14 points. Each item has a different criterion to get 1 point, scoring positively if related to Mediterranean Diet. Thus, a total score of ≤7 indicates low adherence and a total score of > 7 indicates high adherence. We will use a validated Pre-coded Food Record Form to measure food intake in terms of portions consumed [61]. This tool contains the most commonly consumed foodstuffs for the Spanish population. The questionnaire is easy to complete and gives a precise indication of the foods consumed. Participants will fill in this questionnaire crossing out the corresponding boxes and indicating how many portions of each food or food group they consume in a certain day. It includes home examples for portion references in order to facilitate completion. Measurements will be taken at baseline, during the third trimester of pregnancy and after birth (except for the first month) every 2 weeks until the initiation of complementary feeding (4th–6th months after delivery, depending on each participant).Composition profile and rheological characteristics of maternal milk: measured by Infrared Spectroscopy MilkoScan (Foss Electric, Denmark), gas chromatographic- mass spectrometry (GC-MS) and rheometry techniques (rheometer AR1000, TA Instruments). Measurements will be taken during the 2nd month after delivery.Child’s nutritional state: assessed by the periodical paediatric control, reported then by the parents. Assessment will be carried out at the beginning of the weaning process, 6th, 12th and 18th months after delivery.Children Body Mass Index (BMI) from birth: it will be assessed by the periodical paediatric control, and reported by parents at 6th, 12th and 18th months after birth (following the paediatric calendar).Food allergen intake risk during complementary feeding will be assessed taking into account the procedures proposed recently in the scientific literature [62–64] and using self-developed tools for nutrient intake calculation [65].Mother’s psychological state regarding pregnancy: will be assessed by the Prenatal Evaluation Questionnaire [66]. This questionnaire is composed by 42 items divided in 7 dimensions: (1) pregnancy acceptance, (2) identification of the maternal role, (3) quality of the relationship with her mother, (4) quality of the relationship with her partner, (5) preparation for labour, (6) fear to pain and loss of control during labour, and (7) preoccupation for her and her baby’s wellbeing. Possible answers are: A = *a lot*, B = *with frequency*, C = *sometimes*, and D = *never*. Assessment will be carried out at baseline.Maternal anxiety: assessed by the STAI questionnaire (State-Trait Anxiety Inventory) [67]. We will only use the state dimensions in order to assess participant’s anxiety level at the moment the measurements are taken. It is composed by 20 items and answers are given on a 4-point Likert scale (0 = *absolutely not* and 4 = *very much*). Assessment will be carried out at baseline, on the 8th–9th month of pregnancy, on the 4th and 6th month after delivery.Level of depression: assessed by the Edinburgh Postnatal Depression Scale (EPDS) [68]. This questionnaire is composed of 10 items (answered punctuated 0–3 depending on symptoms severity) and will show us the level of the depressive symptoms of the participants. Assessment will be carried out at baseline, on the 8th–9th month of pregnancy and on the 4th and 6th month after delivery.Level of parental stress: assessed by Parental stress scale [69]. It has 17 items with a 5-point Likert scale from 1 = *strongly disagree* to 5 = *strongly agree* and it assesses levels of parental stress. Total score ranges from 0 to 63 and is obtained by the sum of the value for each item. Assessment will be carried out on the 8th–9th month of pregnancy and on the 4th, 6th, 12th and 18th month after delivery.Breastfeeding efficacy and certainty: assessed by the Breastfeeding Self-Efficacy Scale [50]. It has been used to predict breastfeeding duration and exclusivity. It has 14 items and answers are given on a 5-point Likert scale (1 = *not sure at all*, 5 = *completely sure*) and it is one-dimensional. Assessment will be carried out on week 2 after delivery and on the 4th month after delivery.Parental feeding styles: assessed by the Parental Feeding Styles questionnaire [70]. Its 27 items are divided in four subscales: emotional feeding, instrumental feeding, encouragement to eat new foods, and control over eating. Answers range from 1 = *never* to 5 = *always*. Assessment will be carried out on the 6th, 12th and 18th month after delivery.

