#### Intervention group

Baseline questionnaires and initial dietary assessment will be the base for group assignment. Once participants are matched to a group, they will be given a code and will be anonymously treated thereafter. Those above the national (Spain) mean consumption of fruits and vegetables (about 414 g/person/day [58]) will be included in the intervention group. During the study, participants will be encouraged and assessed to achieve even a higher FV intake, following the recommendations given by Aune and colleagues of 800 g/person/day [14]. If a significant decrease in FV intake is detected in the participants' diet during the follow-up visits, dietetic assessment will be performed in order to restore the initial intake. With regard to the weaning groups, those better disposed to follow a baby-led approach will be included in the intervention group.

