#### Control group

Baseline questionnaires and initial dietary assessment will be the base for group assignment and the study participants assigned to the control group will receive the same anonymous treatment as those in the intervention group. Those below the national (Spain) mean consumption of fruits and vegetables (about 414 g/person/day) or/and those who claim to have difficulties achieving the recommended portions will be included in the control group. When a fruit consumption of one standard deviation below the mean is detected, dietetic assessment will be performed in order to encourage, at least, the mean intake. As for the weaning groups, those better disposed to follow a spoon-feeding approach will be included in the control group.

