
### Statistical analysis

#### Quantitative data

The initial analysis of data will be performed on an *intention to treat* basis. A baseline descriptive analysis of the sociodemographic data and measured predictive variables will be carried out to ensure comparability between the intervention and control groups (mothers in the first phase and children in the second phase). Intra-group and inter-group differences in main continuous variables will be analysed by Student’s t test or non-parametric tests (Wilcoxon signed-rank test and Mann–Whitney U test) at different measurement times. For qualitative variables, comparisons will be made using Pearson’s chi square test.

Linear mixed-effects models with participant-level random intercepts will be used to study the effectiveness of the intervention and we will consider adjusting for any demographic or predictive variable results that show important differences at baseline. All statistical analyses will be conducted using the STATA 14.0 and IBM-SPSS 24.0 software. Confidence intervals of 95% and the significance level (*p* values) will be reported.

Subsequent to the initial analysis, we will also carry out a *per protocol* analysis in order to identify possible differences to the intention to treat analysis, which may occur as a result of a differential compliance of participants with the research protocol.

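### Change in maternal fruit and vegetable intake starts from the baseline that sorts mothers into diet groups, so tests of change carry a regression-to-the-mean component of uncertain size

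*Protocol article*

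**What the plan says.** Under Allocation to groups, the Intervention group text states "Baseline questionnaires and initial dietary assessment will be the base for group assignment", and the Control group text repeats this. The rule for the diet arm is "Those above the national (Spain) mean consumption of fruits and vegetables (about 414 g/person/day [58]) will be included in the intervention group". Mothers below that figure go to control, "or/and those who claim to have difficulties achieving the recommended portions will be included in the control group".

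Under Secondary outcomes, the article lists "Change of maternal diet during pregnancy and breastfeeding: measured by the Predimed questionnaire" and by the Pre-coded Food Record Form. On that form mothers mark boxes, "indicating how many portions of each food or food group they consume in a certain day". The timing is: "Measurements will be taken at baseline, during the third trimester of pregnancy and after birth (except for the first month) every 2 weeks", until complementary feeding starts.

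Under Statistical analysis (Quantitative data), "Intra-group and inter-group differences in main continuous variables will be analysed by" t tests or rank tests at the different measurement times. A mixed model with participant random intercepts follows. Adjustment for variables that differ at baseline is something the authors will consider, not something they fix.

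**The concern.** A mother whose recorded intake is high on the day of assessment is partly a mother with high usual intake and partly a mother recorded on a high day. Selecting on the record selects on both parts, and the second does not persist. If change is then measured from the same record, the group above the cut drifts down and the group below drifts up, even when usual intake is constant.

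Maternal diet is the exposure in one of the two main objectives. A biased change outcome could lead the authors to misjudge how well the diet contrast was kept up. The baseline gap between groups would also overstate the difference in usual intake that the infants experienced, if it were read as the exposure. The article does not say that it will be read so.

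**Working it through.** **The plan's own figure.** The article gives no figure for maternal diet. Its sample size (72 per group for 25% versus 50%) concerns the child outcome. It reproduces: 58 per group before dropout, then 58 × 1.2 = 70 or 58 / 0.8 = 73; the arcsine method gives 57.26 / 0.8 = 71.6. It has no bearing here.

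**Inputs.**
- From the article: cut-off c = 414 g/day; HFV target 800 g/day; 144 mothers.
- Assumed, not in the article: observed baseline intake normal with mean μ = 414 and standard deviation s = 200 g/day; reliability r (share of the observed variance due to usual intake) from 0.4 to 0.9; independent error at follow-up; no true change; the sorting value is also the baseline of the outcome.

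**Formula.** With a = (c − μ)/s, and φ and Φ the standard normal density and distribution function:
- expected change above the cut: −(1 − r) · s · φ(a) / (1 − Φ(a))
- expected change below the cut: +(1 − r) · s · φ(a) / Φ(a)

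At a = 0, φ(0)/0.5 = 0.798, so the artefact per group is (1 − r) × 0.798 × 200 = (1 − r) × 159.6 g/day.

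| r | HFV (g/day) | SD (g/day) | Difference in change (g/day) |
|---|---|---|---|
| 0.4 | −96 | +96 | 191 |
| 0.5 | −80 | +80 | 160 |
| 0.7 | −48 | +48 | 96 |
| 0.9 | −16 | +16 | 32 |

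**Sensitivity.** Over means of 350 to 480 g, standard deviations of 150 to 250 g and r from 0.3 to 0.9, HFV falls by 8 to 169 g and SD rises by 8 to 170 g. The signs of the artefact never change.

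**Assignment that is not a pure cut.** Simulation with 144 mothers and r = 0.5 gave −79 and +79 g. Moving a random 20% of the mothers above the cut to control, to mimic claimed difficulties, gave −80 and +53 g. The SD artefact shrinks because SD then includes some mothers who drift down.

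**Effect on the tests.** With a pure cut and no true change, the between-group t test of change at the 5% level rejected in about 100%, 97% and 55% of runs at r = 0.5, 0.7 and 0.9. Regressing follow-up intake on group and baseline intake brought rejection back to about 5%, with a spurious group effect near zero.

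**Baseline gap.** The observed gap between groups is 2 × 159.6 = 319 g/day. The gap in usual intake is r times that: 128 g at r = 0.4 and 287 g at r = 0.9.

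**Set against successful coaching.** The observed HFV baseline mean is 414 + 159.6 = 574 g/day. If the group reached 800 g/day, the recorded rise would be 800 − 574 = 226 g. The true rise would be larger by the artefact: 226 + 96 = 322 g at r = 0.4, or 226 + 16 = 242 g at r = 0.9.

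**The case against.** Several points on the other side stand.

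- **The shared measurement is inferred.** The article nowhere says that the 414 g/day comparison uses the Food Record Form baseline. Assignment rests on baseline questionnaires and a dietary assessment, and no other maternal diet tool is named, so the inference is fair. If sorting used a separate record with independent error, the artefact would largely vanish.
- **The noise is assumed.** Wording about a certain day describes how one form is filled in, not how many days make up the baseline. A condensed article may omit that number, and it calls the form validated. With good reliability the artefact is small.
- **Assignment also uses likings, type of diet and claimed difficulties**, which dilutes the effect in SD.
- **The g/day figures do not apply to the Predimed score**, a 0 to 14 score for the whole diet. It is affected only as far as its error correlates with that of the sorting measure.
- **Comparisons at post-assignment times and baseline adjustment are not excluded.** But the adjustment is only to be considered, and a random-intercept model that treats baseline as one of the repeated outcomes does not remove the artefact.

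A reader might infer that HFV mothers will appear to fail and controls to improve even if coaching works. The article does not support that. On the assumptions above, reaching the target still shows a rise of about 226 g. A false fall needs true intake to stay flat or to rise by less than the artefact. Encouragement towards higher intake in HFV, and towards the mean in low-intake controls, adds real change, so net changes need not be opposite.

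**Conclusion.** The point holds in a limited form. Where the sorting measure and the food-record baseline share error, change in maternal fruit and vegetable intake contains a component that is downward in HFV and upward in SD for any reliability below 1. It attenuates or masks a real rise in HFV and inflates one in SD. The direction follows from the design; the size does not. With a standard deviation of 200 g/day, a cut at the mean and reliability 0.4 to 0.9, it is about 96 down to 16 g/day per group, and less in SD if mothers above the cut are placed there for claimed difficulties.

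It would go too far to infer bias in the primary child outcomes: they are not change scores from this maternal baseline. The problem is confined to one component of a secondary outcome, but the correction is cheap enough to be worth making.

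**What to change.** 1. State which record is used for assignment, and use it for classification only.
2. Define the maternal fruit and vegetable outcome as mean intake over the scheduled post-assignment records: before delivery, then every 2 weeks after the first postnatal month.
3. Report the HFV minus SD contrast on that mean beside the child outcomes as the exposure delivered. Say that it describes exposure and is not an effect of coaching, since the groups were selected on intake.
4. If change from baseline is also reported, do not compare groups by unadjusted change tests. Condition on the baseline intake used for assignment, and state that within-group changes include regression to the mean. This adjustment is cleanest when assignment depends only on measured intake; claimed difficulties related to usual intake would leave some residual bias.

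Simply starting change from the third-trimester record is not a safe substitute. The first information session comes before the third trimester, so early coaching effects could be lost, and the timing sentence can be read as making baseline and third trimester one occasion.

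The cost is wording and one model term; the records are already scheduled. The reported diet contrast may be smaller than at baseline, and the post-assignment mean alone does not show change.
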